# Effects of modified-Paleo and moderate-carbohydrate diets on body composition, serum levels of hepatokines and adipocytokines, and flow cytometric analysis of endothelial microparticles in adults with metabolic syndrome: a study protocol for a randomized clinical trial

**DOI:** 10.1186/s13063-021-05612-y

**Published:** 2021-09-30

**Keywords:** Randomized control trial, Metabolic syndrome, Low-carbohydrate diet

## Abstract

**Background:**

Metabolic syndrome is a combination of metabolic risk factors causing a pathological condition that increases the risk of non-communicable diseases, such as diabetes and cardiovascular diseases. A variety of dietary approaches have been examined to halt this rapid trend; however, the effects of modified-Paleo diet and medium-carbohydrate diet on inflammation, adipokines, hepatokines, and the profile of endothelial microparticles in individuals with metabolic syndrome have not been investigated in detail. The present study is designed to examine the effect of modified-Paleo and moderate-carbohydrate diet with two delivery modes: “fixed diet plan” vs “calorie counting” on weight, body composition, serum levels of some hepatokines and adipocytokines, and flow cytometric analysis of endothelial microparticles in adults with metabolic syndrome.

**Methods:**

Eighty metabolic syndrome patients will be recruited in this study. They will be randomly allocated to one of the following 4 groups: (1) receiving a modified-Paleo diet with calorie counting, (2) receiving a modified-Paleo diet with a fixed diet plan, (3) receiving a medium-carbohydrate diet with calorie counting, and (4) receiving a medium-carbohydrate diet with a fixed diet plan for 10 weeks. Weight, height, waist circumference, and body composition will be assessed at the study baseline and at the end of the trial. Serum insulin, asprosin, chemerin, FGF-21, CTRP-1, PYY, ghrelin, plasma EMPs (CD31+/CD42b− and CD144+/CD42b−), lipid profile, glycemic indices, hs-CRP, leptin, vitamin C, creatinine and satiety, hunger, fullness, and desire to eat (via visual analog scales) will be measured at the study baseline and at the end of the trial. Insulin resistance and insulin sensitivity will be determined using the HOMA-IR and QUICKI equations.

**Discussion:**

To the best of our knowledge, this is the first randomized controlled trial that will determine the effect of modified-Paleo and moderate-carbohydrate diet on weight, body composition, serum levels of some hepatokines and adipocytokines, and the profile of EMPs in adults with metabolic syndrome. Moreover, the effects of different diet delivery modes, including “fixed diet plan” and “calorie counting” will also be analyzed. The results of this trial can provide clinical witnesses on the effectiveness of carbohydrate-restricted diets in ameliorating metabolic status and prevent the development of chronic diseases.

**Trial registration:**

Iranian Registry of Clinical Trials IRCT2016121925267N4. Registered on 26 July 2017

**Supplementary Information:**

The online version contains supplementary material available at 10.1186/s13063-021-05612-y.

## Background

Metabolic syndrome is defined as a set of inter-related risk factors including abdominal obesity, hypertension, impaired glucose tolerance, and dyslipidemia. While each of the underlying disorders of metabolic syndrome intensifies the risk of various non-communicable diseases [1], their co-occurrence increases the risk of further complications and mortality [2]. The prevalence of this disorder varies between 14 and 32% globally. Based on the evidence, this syndrome occurs among one-third of adults in Iran [3]. A nutritional transition may be the reason for this high rate of prevalence in Iran which may be resulted from a shift from a traditional diet towards a Western-style diet [4, 5].

Among several attributable risk factors to this public health issue according to almost all of the proposed definitions [6], obesity and insulin resistance are seemed to be the cornerstones of most of the cases of metabolic syndrome [7]. Accordingly, lifestyle alteration such as dietary modifications is still considered the mainstay of treatment to induce weight loss and ameliorate symptoms of metabolic syndrome upon the emergence of its consequences like CVD [8]. Yet, no ideal dietary strategy is consistently superior to others for the general population.

The composition of macronutrients plays a pivotal role in diet recommendations. Conventional low-fat diets have been the most usual dietary strategy for weight reduction for many years, although low-carbohydrate diets with continued success are receiving more attention and popularity in recent years [9]. Despite the fact that low-carbohydrate diets are still controversial, they still are effective with minimum risk and acceptable compliance. A new evaluation on a low-carbohydrate diet is necessary because of several side effects of anti-obesity medications and unacceptable approaches regarding low-fat and energy-restricted diets. One important concern in the field of low-carbohydrate diets is the definitions for this diet.

As mentioned earlier, metabolic syndrome is a chronic and progressive clustering of synergistic metabolic risk factors, which makes the individual more prone to develop especially cardiovascular diseases, approximately twice more than those not having it. Although the particular mechanism of metabolic syndrome pathogenesis has not been understood in detail, researches have shown that biological mediators, known as adipocytokines, produced by adipose tissue contribute to the development of metabolic syndrome [10].

Moreover, the liver plays a role in regulating whole-body metabolism and energy homeostasis via liver-derived proteins known as hepatokines. Hence, hepatokines, besides being valuable predictive biomarkers, could be considered as potential targets for the treatment of cardio-metabolic disorders [11].

Microparticles are cell membrane-shedded fragments, usually expressed by cells during cellular stress and cell activation. Microparticles have a role in the pathogenesis of inflammation [12], cardiovascular diseases [13], and metabolic syndrome [14] and are biomarkers for assessing endothelial function in metabolic syndrome [15].

As carbohydrate-restricted diets have shown to influence inflammation and body composition [16], it is hypothesized that they might affect the level of adipo- and hepatokines and also the level of endothelial microparticles in patients with metabolic syndrome. This factorial design randomized clinical trial is therefore designed to examine the effect of modified-Paleo and moderate-carbohydrate diets with two delivery modes (“fixed diet plan” and “calorie counting”) on weight, body composition, serum levels of some hepatokines and adipocytokines, and flow cytometric analysis of endothelial microparticles in adults with metabolic syndrome.

## Methods/design

This randomized single-blind clinical trial with a factorial design will be conducted in Tehran, Iran. All participants will be asked to complete and sign the written informed consent form before enrollment. The study has already been approved by the bioethics committee of Tehran University of Medical Sciences (No. IR.TUMS.VCR.REC.1396.2046).

### Study population

The current RCT is a community-based participatory research. Participants will be recruited through a well-known online advertising application rather than relying on one health care center or hospital. This was done with the aim of reflecting the diversity of the population and reaching more generalizable conclusions.

### Inclusion criteria

In this study, we will recruit 20–60-years-old patients with metabolic syndrome, at least 1–2 weeks prior to enrollment. Diagnosis of metabolic syndrome will be made based on NCEP-ATPIII [17]. Patients will be recruited if they had at least 3 out of 5 of the abovementioned factors.

### Exclusion criteria

Individuals who are smokers, those consuming alcohol, are pregnant or lactating, or decided to get pregnant during the next 3 months will not be included. Moreover, individuals with some pathologic conditions including cancer, any acute or chronic liver failure, and liver transplantation; suffering from diabetes, heart failure, renal failure, inflammatory disease, and chronic gastrointestinal diseases; usual consumption of corticosteroids and non-steroidal anti-inflammatory drugs (NSAIDs); hormone replacement therapy (HRT); or those taking high dosage of estrogen, insulin, usual receiving of herbals, antioxidant, and multivitamin/mineral supplements during the last 3 months will not be included.

### Study design

At the initial phase, 100 patients with metabolic syndrome will be screened based on the inclusion criteria mentioned above. Subjects recruited through online advertisements and social media and those who meet the criteria will be included and are randomly assigned in one of the following 4 groups: (1) those receiving a modified-Paleo diet with calorie counting, (2) receiving a modified-Paleo diet with a fixed diet plan, (3) receiving a medium-carbohydrate diet with calorie counting, and (4) receiving a medium-carbohydrate diet with a fixed diet plan. The principal investigator ([name]) will recruit eligible participants and obtain a consent form. In the consent form, participants will be informed of the study interventions, duration, and contact details of the research team in case of any question. Participants will be told that all health services are free of charge, and they can withdraw their consent at any time of the study. Participants will be told that their participation is on a voluntary basis, and they are required to sign the consent form prior to any data collection. Before allocating participants into the four intervention groups, anthropometric indices including weight, height, and waist circumference (WC) will be measured, and body mass index (BMI) will be calculated. Body composition will be assessed by bioelectric impedance analysis (BIA) according to the instrument instructions. Individual questionnaires including socio-demographic characteristics, past medical, drug and diet history, and validated International Physical Activity Questionnaire (IPAQ) will be also completed for each patient through a comprehensive face-to-face interview. Each individual will be given a booklet consisting of a pre-designed diet program and a series of recipes, meal plans for breakfast, lunch, dinner, and snacks according to the given diet. Those receiving the fixed diet plan method will be provided with special measuring cups with definite colors for each food group. Subjective appetite rating will be assessed by visual analog scales (VAS) to evaluate satiety, hunger, fullness, and desire to eat. To fulfill this, a VAS questionnaire will be given to each participant to fill them every 2 weeks at home. Finally, to perform biochemical measurements, 10-ml overnight fasting venous blood samples will be collected from each participant, and to isolate circulating EMPs from platelet-poor plasma (PPP), 5 ml of venous citrated blood will be obtained from each patient. All personal information of the participants will be confidential in the whole study. Outcome assessors will be blinded to the intervention assignments in the current study. A diagram of the study design is shown in Fig. 1.

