### Study outcomes

In the present study, we have multiple primary outcomes due to the nature of the dietary interventions as seen in many other randomized clinical trials [18, 19]. A single outcome may be insufficient to fully describe the effects of an intervention on a complex disease, namely metabolic syndrome. Weight, body composition, and CTRP6 (as an inflammatory marker) are the main primary outcomes in the current study. Sample size calculation has been estimated on the body weight changes as the largest number achieved in each group. Hence, our primary endpoints will be the mean difference in the changes from baseline to 10-week follow-up in body composition component (weight and body fat mass) and CTRP6 concentration between the intervention groups. Study success will be declared if either one of the primary endpoints will be statistically significant in favor of the experimental treatment.

The main secondary outcomes would be lipid profile, glycemic indices, serum insulin, leptin, and plasma EMPs (CD31+/CD42b− and CD144+/CD42b−). Satiety, hunger, fullness and desire to eat [20], inflammatory factors (chemerin, FGF-21, Asprosin), PYY, ghrelin, and creatinine are exploratory outcomes.

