### Sample size

We calculated the required sample size based on data from a previous study [21]. Sample size calculation was performed with the G*Power V.3.1.9.2 software [22], using the *F* test between the factors with four groups (modified-Paleo diet with calorie counting, modified-Paleo diet with a fixed diet plan, medium-carbohydrate diet with calorie counting, and medium-carbohydrate diet with fixed diet plan) and two evaluation sessions (before and after intervention). According to the mean difference in the change in body weight (11 kg) and standard deviation of 15 (by assuming equal standard deviation in groups) [21], the calculated effect size *f* is 0.39. We considered an *α* error probability of 0.05 and a power (1-*β* error probability) of 0.80. We take the correlation among repeated measures as 0.6. The resulting total sample size is 60, meaning 15 in each intervention group. Allowing for a maximum dropout rate of 30%, the final number of subjects in each treatment group has been set to 20 participants. The study is registered on the Iranian Registry of Clinical Trials website (http://www.irct.ir, identifier: IRCT2016121925267N4). This study was reported based on the recommended checklists for clinical trials [23, 24] (Additional file 1).

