### Outcome measurements

The time points for the assessments of the outcome measures are demonstrated in Fig. 2. All outcome measures will be assessed at the study baseline and at the end of 10 weeks (WK10). Dietary intakes will be assessed at the study baseline, in the middle of the study (WK5), and at the end of 10 weeks (WK10).

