### Statistical analysis

Statistical analyses of all data will be performed using STATA version 12.0 (Stata Corp LP, College Station, TX). The intention-to-treat approach will be used for data analysis in order to handle non-adherence. Data will be expressed as mean (SD). The one-sample Kolmogorov–Smirnov test will be used to verify the normality. If a variable distribution is not normal, the log transformation will be applied. An analysis of variance (ANOVA)/analysis of covariance (ANCOVA) model will be used to compare the values among the four intervention groups. Analysis of variance (ANOVA) and post hoc Bonferroni correction will be used for multiple comparison adjustment. Since we have 4 intervention groups (1, modified-Paleo diet with calorie counting; 2, modified-Paleo diet with a fixed diet plan; 3, medium-carbohydrate diet with calorie counting; and 4 medium-carbohydrate diet with a fixed diet plan), we will have six possible pairwise comparisons across the groups (1 with 2, 1 with 3, 1 with 4, 2 with 3, 2 with 4, 3 with 4). By these primary comparisons, we will be able to compare the effects of diets (low vs moderate carbohydrate) and delivery modes (calorie counting vs fixed diet plan) on primary outcomes. Further, there are two modules, by which confidence intervals can also be adjusted along with *p*-value for multiple comparisons. “Pwmean” and “pwcompare” modules allow for performing all pairwise comparisons using Tukey, Bonferroni, or Dunnett. An analysis of covariance (ANCOVA) will be applied to adjust the effects of confounding and baseline variables. *p* < 0.05 (two-sided) will be considered as statistically significant. Besides the null hypothesis significance testing (NHST), appropriate effect size and its 95% confidence interval will also be analyzed to provide more reasonable justification about results. Cohen’s *d* effect size, measured as the mean difference in change divided by the pooled standard deviation of the change, will be reported along with its 95% CI. Cohen’s *d* is defined as standardized mean difference (SMD) and is classified as small (*d* = 0.2), medium (*d* = 0.5), or large (*d* = 0.8) [27]. Multiple imputation will be used to correct missing data. The SAMPL guideline will be used for statistical analysis in this study [28].

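### Appetite VAS is collected every 2 weeks but scheduled elsewhere at baseline and week 10 only; as written, the interim readings have no stated place in the analysis of this exploratory outcome

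*Protocol article*

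**What the plan says.** Three places in the protocol article give the timing of the appetite scales (satiety, hunger, fullness, desire to eat), and they do not agree.

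- Study design has the forms filled in repeatedly during follow-up: "a VAS questionnaire will be given to each participant to fill them every 2 weeks at home".
- The Abstract, under Methods, names the scales and gives two time points: "desire to eat (via visual analog scales) will be measured at the study baseline and at the end of the trial".
- Outcome measurements gives two time points for everything: "All outcome measures will be assessed at the study baseline and at the end of 10 weeks (WK10". The sentence after it adds a single interim assessment, at week 5, for dietary intake. The VAS is not mentioned as an exception.

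Study outcomes places the four scales among the outcomes, at the lowest (exploratory) tier. So the statement about every outcome covers them.

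On analysis, the article says that an ANOVA/ANCOVA "model will be used to compare the values among the four intervention groups". It adds that ANCOVA adjusts for baseline variables and that Cohen's d is computed on change. Missing data are to be handled by multiple imputation. The sample size, worked out for body weight, assumes "two evaluation sessions (before and after intervention". No longitudinal model or summary of interim readings is named.

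**The concern.** A reader cannot tell from the article how many VAS readings each participant will have, or which of them count as the outcome. Taken literally, the Abstract and Outcome measurements make this a two-point outcome, while Study design has participants filling in forms at home throughout the 10 weeks. The interim forms would then be a burden on participants with no declared use.

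Two things are at stake, both modest. First, someone who leaves at week 9 may already have supplied several on-diet readings, and a two-point analysis would take nothing from them. Second, with four scales and several possible time points, an unsettled schedule leaves open which reading or summary is reported once the data have been seen.

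**Working it through.** **1. Plan's own figure.** There is none for the VAS. The stated total of 60 and the correlation of 0.6 are for body weight. Using 0.6 for the VAS is an assumption, so a range of 0.4 to 0.8 is shown.

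**2. Share of readings.** Every 2 weeks over 10 weeks is read here as weeks 2, 4, 6, 8 and 10, which the article does not list. If only week 10 is analysed, 4/5 = 80% of on-diet readings are left out. With 80 participants and no dropout that is 4 × 80 = 320 of 5 × 80 = 400, an upper limit because dropout is expected.

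**3. Variance of two different targets.** Take the variance of one reading as 1 and assume equal correlation r between any two readings. Adjusted for baseline:

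- week 10 alone: 1 − r²
- mean of five on-diet readings: (1 + 4r)/5 − r²

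| r | Week 10 | Mean of five | Ratio | Reduction |
|---|---|---|---|---|
| 0.4 | 0.84 | 0.36 | 0.43 | 57% |
| 0.6 | 0.64 | 0.32 | 0.50 | 50% |
| 0.8 | 0.36 | 0.20 | 0.56 | 44% |

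If correlation instead decays over time (AR(1), 0.6 to 0.9 per 2-week step), the ratio is 0.45 to 0.49.

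**4. Does smaller variance mean more sensitivity?** That depends on how the effect develops. The information ratio of the average against week 10 is (average effect ÷ week-10 effect)² ÷ variance ratio.

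- Constant effect: 1/0.43, 1/0.50 and 1/0.56, or about 2.3, 2.0 and 1.8, favouring the average.
- Effect building linearly (0.2, 0.4, 0.6, 0.8 and 1.0 of its final size, an assumption): the average effect is 0.6 of the week-10 effect and 0.6² = 0.36. The ratios are 0.36/0.43 = 0.84, 0.36/0.50 = 0.72 and 0.36/0.56 = 0.65, favouring week 10.
- Break-even: the average effect must be at least √0.43 = 0.65, √0.50 = 0.71 or √0.56 = 0.75 of the week-10 effect.

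**5. Gain for the week-10 difference itself.** With complete data, interim readings add essentially nothing. They help where week 10 is missing. As a favourable case, suppose that 30% miss week 10 only, at random. Given baseline and the four interim readings, the week-10 residual variance is 1 − 5r²/(1 + 4r) = 0.69, 0.47 and 0.24 for r = 0.4, 0.6 and 0.8. Against the baseline-only values in step 3, the interim readings explain 1 − 0.69/0.84 = 0.18, 1 − 0.47/0.64 = 0.26 and 1 − 0.24/0.36 = 0.34 of what remains. The variance of the week-10 difference is multiplied by 1 − 0.30 × that share = 0.95, 0.92 and 0.90. The gain is therefore about 5 to 10%. It would be smaller if people leave earlier and larger if neighbouring readings are more strongly correlated than distant ones.

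**The case against.** The strongest reply is that the article never says that the interim readings will be dropped. A reader might infer that four fifths of the data go unused, but neither the Abstract nor Outcome measurements says that the VAS is measured at those two times only. The schedule figure to which Outcome measurements refers is not available here. The named ANCOVA could be run on the mean of all on-diet readings. How an exploratory repeated measure is summarised is commonly left to an analysis plan. All of this stands, so the absence of a longitudinal model is not in itself an error.

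A reader might also infer that the planned analysis wastes about half of the available precision. The documents do not support that. The halving compares a week-10 difference with an average on-diet difference. It rests on an assumed VAS correlation, and it turns into a gain in sensitivity only under a roughly constant effect. Week-10 change is the target that the article sets for its primary endpoints.

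Nor are early leavers simply lost, since intention to treat and multiple imputation are specified. The article does not say when the home forms are returned, so how many readings dropouts will have supplied is unknown.

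The timing conflict survives these replies. An article that makes an explicit interim exception for diet but not for the VAS, and that gives two time points for the VAS by name, does not agree with fortnightly collection.

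**Conclusion.** The point holds as a small one. The VAS schedule in Study design conflicts with the Abstract and with Outcome measurements. If the latter two and the named ANOVA/ANCOVA are followed, the readings before week 10 would not enter the analysis.

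For week 10, the benefit of using them comes mainly through dropouts: roughly 5 to 10% in variance in the favourable case worked above, under equal correlation. For the on-diet average the variance is 44 to 57% smaller, but that answers a different question. All of these sizes rest on assumed correlations, because the article gives none for the VAS. The outcome is exploratory, so nothing confirmatory is affected. This is a cheap improvement and not a defect that threatens the trial.

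**What to change.** 1. Reconcile the Abstract, Study design and Outcome measurements (and the schedule figure, if it differs) to one VAS schedule, listing the weeks.
2. Analyse all on-diet readings of each scale in a linear mixed model adjusted for baseline VAS, with diet, delivery mode, week and the interactions of diet and delivery mode with week. Keep the week-10 difference, for consistency with the other outcomes, and report the average on-diet difference alongside. State both before the data are seen.
3. If the simpler ANCOVA is preferred, at a minimum put the interim readings into the multiple imputation model.

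The cost is a corrected sentence in each place and a little more analysis work. No extra data are collected, and no primary endpoint, sample size or success rule changes.
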